# Comparing the effectiveness of selective laser trabeculoplasty with topical medication as initial treatment (the Glaucoma Initial Treatment Study): study protocol for a randomised controlled trial

**DOI:** 10.1186/s13063-015-0924-6

**Published:** 2015-09-11

**Keywords:** Glaucoma, eye drops, selective laser trabeculoplasty, quality of life, cost-effectiveness, randomised clinical trial

## Abstract

**Background:**

Glaucoma is the leading cause of irreversible blindness in the world. Estimated to affect 60 million people worldwide, this figure is expected to rise to 80 million by 2020. Untreated, glaucoma leads to visual decay and eventually to blindness, and can significantly reduce quality of life. First-line treatment in patients with primary open-angle glaucoma and exfoliative glaucoma is topical medical therapy with ocular hypotensives as eye drops. However, eye drops have several disadvantages including cost, possible local and systemic side effects, and adherence and perseverance issues. Randomised controlled trials have demonstrated that selective laser trabeculoplasty is equally as effective in lowering intraocular pressure as eye drops. However, the impact of these two treatment modalities from the patient and economic perspectives has not been adequately determined. Thus, it remains unclear whether topical medical therapy or selective laser trabeculoplasty should be recommended as first-line treatment for glaucoma.

**Methods/Design:**

This protocol describes an international, multi-centre, randomised controlled trial to determine the optimum first-line therapy for people with primary open-angle glaucoma and exfoliative glaucoma. This study will compare the effect of selective laser trabeculoplasty and topical medication with respect to patients’ generic and glaucoma-specific quality of life. The trial will also provide a detailed cost-effectiveness analysis and compare the clinical effectiveness with respect to the degree of intraocular pressure lowering and rates of treatment failure. Research coordinators in each centre will identify and recruit previously untreated patients with primary open-angle glaucoma and exfoliative glaucoma. Those who meet the eligibility criteria will be invited to enter a randomised controlled trial with either selective laser trabeculoplasty or topical ocular hypotensive therapy, according to a stepped regimen. Outcome assessment will be measured at 6 weeks and at 6, 12, and 24 months post-treatment. Regular clinic follow-ups will continue as clinically indicated between study outcome visits.

**Discussion:**

The Glaucoma Initial Treatment Study is the first multi-centred RCT to determine the optimum first-line therapy for people with glaucoma. Our trial will have an unprecedented capacity to meaningfully transform the treatment and management of glaucoma in Australia and overseas.

**Trial registration:**

ACTRN12611000720910; Date registered: 11 July 2011

## Background

Glaucoma is the leading cause of irreversible blindness in the world [1]. Estimated to affect 60 million people worldwide, this figure is expected to rise to 80 million by 2020 [2]. Glaucoma represents a group of optic neuropathies characterised by a progressive degeneration of retinal ganglion cells and their axons resulting in structural changes of the optic nerve and retinal nerve fibre layer with concomitant patterns of visual loss. Untreated, glaucoma leads to visual decay and eventually to blindness, although less severe glaucoma can also significantly reduce quality of life (QoL) and cause economic burden to both the individual and society [3–5].

The pathophysiology and factors contributing to the onset and progression of glaucoma are not fully understood. Reduction in intraocular pressure (IOP) is the only modifiable risk factor known to delay glaucoma onset and progression [6]. IOP is regulated by a balance between the rates of aqueous humour secretion by the ciliary body epithelium and its drainage via the trabecular meshwork and uveoscleral outflow pathways. First-line treatment in patients with glaucoma is topical medical therapy with ocular hypotensives as eye drops. These either increase the aqueous outflow (such as prostaglandin analogues) or reduce aqueous production (such as beta-adrenergic antagonists). Topical medical therapy effectively lowers the IOP [6] but has limitations and disadvantages including cost, possible local and systemic side effects, adherence and perseverance issues, physical barriers to self-instillation (such as tremor or arthritis) and the prospect of daily and often life-long commitment to medications [7–21].

The use of laser trabeculoplasty to lower IOP has provided an alternative strategy to treat glaucoma. One of the laser trabeculoplasty modalities is selective laser trabeculoplasty (SLT), which utilises a Q-switched, frequency-doubled Nd:YAG (532 nm) laser. It lowers IOP in patients with glaucoma by enhancing aqueous outflow through the trabecular meshwork, but the exact mechanism underlying the effectiveness of SLT remains uncertain. SLT has been shown to recruit monocytes to the trabecular meshwork and induce disassembly of tight junctions in Schlemm’s canal cells [22, 23]. In comparison with older laser trabeculoplasty techniques, SLT induces less coagulative damage and structural change to the meshwork and is potentially repeatable [24]. However, the effect of SLT diminishes over time and it may be associated with local adverse effects such as post-laser inflammation and temporary elevations in IOP.

Studies comparing these treatments have demonstrated no significant differences between prostaglandin eye drops and SLT in lowering IOP [25, 26], although one study showed that the prostaglandin analogue latanoprost controlled IOP fluctuations better than SLT [27]. From the societal perspective, a published cost-analysis found SLT to be less costly than most brand-name topical medications within 1 year and less costly than generic latanoprost and generic timolol (beta-adrenergic antagonist) after 13 and 40 months, respectively [28].

Although these studies have indicated that SLT and topical prostaglandins are equally effective in lowering IOP, they were generally underpowered and did not consider the impact of these two treatment modalities from the patient and economic perspectives. Glaucoma patients can experience reduced QoL due to associated functional loss; emotional and social implications; and the inconvenience, side effects and cost of treatment [3, 4, 29–34]. Thus, it remains unclear whether topical medical therapy or SLT should be recommended as first-line treatment for glaucoma with corresponding improvements in QoL and economic benefits.

### Objectives and hypotheses

We are implementing a multi-centre randomised controlled trial (RCT) to determine the optimal first-line therapy for people with primary open-angle glaucoma (POAG) and exfoliative glaucoma (XFG). Our primary endpoint will be health-related QoL (HRQOL). This study will evaluate treatment outcomes with respect to patient QoL, provide a detailed economic effectiveness analysis, and compare the clinical effectiveness in terms of the degree of IOP lowering and rates of treatment failure.

We hypothesise that treatment with SLT, compared with topical medication, will improve overall and glaucoma-specific QoL parameters, show comparable IOP reduction and demonstrate less ocular and systemic side effects, including less frequent ocular surface disease. We postulate that SLT treatment is more cost-effective than topical medical therapy in the treatment of POAG and XFG.

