### Specific aims

Aim 1: Our first aim is to compare the effect of SLT and topical medication on glaucoma-specific QoL at 6 weeks and at 6, 12, and 24 months post-treatment (primary outcome).

Aim 2: Our second aim is to quantify the cost-effectiveness of SLT treatment compared with glaucoma medication treatment.

Aim 3: Our third aim is to determine factors associated with treatment outcomes at 12 and 24 months post-SLT, including the rate of IOP success, defined as >25 % reduction in IOP from baseline measurements.

Aim 4: Our final aim is to assess the impact of SLT and eye drops on safety, laser-linked complications, and common side effects for glaucoma patients after the initiation of treatment.

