### Topical ocular hypotensive therapy

Patients randomised to the topical medication treatment group will be initially prescribed, where possible, a prostaglandin analogue with one drop to be instilled in each eye (or the study eye only if only one eye is enrolled) once daily (Fig. 2). We will instruct patients on how and when to instil their drops and stress the importance of adherence. Patients will return for review of treatment response 6 weeks from the baseline initiation of treatment and will follow a stepped regimen, depending on their response. We will change treatment if there is an adverse event that is considered severe enough to warrant such change or if there is progression in visual field loss or optic disc changes. Treatment response will be defined as follows:Successful response ≥25 % IOP reduction compared with baselines.Partial response = 10-25 % IOP reduction compared with baselines.No response = ≤10 % IOP reduction compared with baselines.

If patients have crossed over with both treatment regimens, they will exit the trial with further management at the discretion of the treating doctor (Figs. 1 and 2).

Based on the grading system developed by the Collaborative Initial Glaucoma Treatment Study (CIGTS) [35], optic discs will be clinically analysed for the following characteristics: (a) vertical and horizontal central cup to disc ratio; (b) focal and diffuse thinning of neuro-retinal rim; (c) presence of a disc haemorrhage; (d) nerve fibre layer defects; and (e) extent of peripapillary atrophy. If a change in treatment is deemed necessary and urgent, it may be initiated by the site investigator although the images would be reviewed by the Optic Disc Outcomes Committee (ODOC), masked to the treatment allocation (and initially the temporal sequence of the photos) to validate treatment change. For all disc changes considered non-urgent, these images will be referred to the ODOC where it will be the final arbiter on the presence/absence of optic disc changes and any alteration to treatment regimens. Visual field progression will be defined according to the following criteria identified by the Glaucoma Progression Alert on the Humphrey Visual Field result:Possible progression = 3 or more points show deterioration on at least 2 consecutive visits.Likely Progression = 3 or more points show deterioration on at least 3 consecutive visits.No progression detected = none of the above conditions is met.

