#### Clinical

Clinical secondary outcomes will be determined by the success rates of IOP reduction (defined as >25 % fall in IOP from baseline), changes in the visual field and optic disc from baseline to 24 months. The times required to reach these changes will be reported. Changes in the optic nerve head will be based on rim thinning, haemorrhage, or an increase in cup to disc (C/D) ratio and visual field changes based on progression.

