#### Clinical efficacy

To assess clinical efficacy (IOP reduction success), Chi square tests will be used and multivariable logistic regression models with odds ratios (OR) and 95 % CI will be built. Other analyses will be tailored to the nature of the secondary outcome data. Numerical data (for example, IOP and visual acuity) and dichotomous data (presence/absence) will be analysed by the GEE. Survival data (for example, time-to-VF (visual field) progression, IOP becoming uncontrolled again) will be analysed using survival analysis. Stepwise multiple regression analyses for secondary outcomes will evaluate a similar set of potential explanatory factors (covariates) in addition to treatment assignment and those evaluated for the primary analysis. Time-varying covariates will be used for analyses evaluating repeated measures of the outcome, if appropriate. Standard errors of estimates from log-linear models will take account of possible over-dispersion with respect to the assumed models.

To determine the impact of SLT (single or multiple applications) on safety, surgical complications, and common side effects associated with glaucoma treatment, Chi square tests will be used initially and regression models with ORs and 95 % CI will be built. Where appropriate, Poisson regression will be used to compare event rates (for example, adverse events). To determine the predictors of IOP reduction success, survival curves will be constructed using the Kaplan-Meier method. Cox proportional hazards method will be used to adjust for confounders. Hazard ratios (HR) with 95 % CI will be provided to estimate the relative risk.

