### Sample size estimation

The sample size for the study is based on the primary outcome measure of HRQoL at 24 months post-treatment. Our hypothesis is that compared with topical medication, SLT treatment will have a significantly greater positive impact on HRQoL. Mean and standard deviations for the pilot data of GOAT and previous work with the Glau-QoL were used [36, 38]. To detect a 0.156 Logit difference (effect size of 0.3) on the Rasch-analysed GOAT and Glau-QoL at 80 % power with a 5 % level of significance, 175 patients will be needed in each group. Similarly, the mean and standard deviation values for the AQoL-7D were obtained from the literature [39, 47]. To detect a 0.7 difference (effect size of 0.3) on the AQoL-7D between the two groups at 24 months with 80 % power at 5 % level of significance; 176 patients will be needed for each group. Assuming an attrition rate of 15 % after 2 years, 193 patients will be enrolled in each group at baseline. Furthermore, for Aim 3, the study will also have 79 % power to detect a 10 % difference in ‘success rate’ of IOP (defined as ≥25 % reduction in baseline IOP) in the SLT group compared with topical medication using a two-sided log-rank test at the 5 % significance level.

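### IOP success is defined both as more than 25 % and as at least 25 %, and the hypothesis of comparable IOP reduction is matched only to tests of difference, with no margin

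*Protocol article*

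**What the plan says.** **Definition of success.** Four places in the protocol article give a cut-off.

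- Specific aims, Aim 3: "including the rate of IOP success, defined as >25 % reduction in IOP from baseline measurements".
- Outcome measures, Clinical: "defined as >25 % fall in IOP from baseline".
- Sample size estimation, in the power statement for the same Aim 3: "defined as ≥25 % reduction in baseline IOP) in the SLT group compared with topical medication using a two-sided log-rank test".
- Topical ocular hypotensive therapy, where response decides the next treatment step: "Successful response ≥25 % IOP reduction compared with baselines", followed by "Partial response = 10-25 % IOP reduction compared with baselines". The third band, no response, is a fall of 10 % or less.

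**Hypothesis and tests.** Objectives and hypotheses expects SLT to "show comparable IOP reduction and demonstrate less ocular and systemic side effects". The Statistical analysis plan section sets every test at the 5 % two-sided level. Clinical efficacy says "To assess clinical efficacy (IOP reduction success), Chi square tests will be used", and adds logistic regression with odds ratios and 95 % confidence intervals, GEE for numerical IOP, and Kaplan-Meier and Cox methods for predictors of success. The only power figure for IOP is 79 % to detect a 10 % difference in success. No equivalence or non-inferiority margin appears.

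**The concern.** Two separate defects meet in one secondary outcome.

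First, the outcome is defined one way and powered another. A patient whose IOP falls by exactly 25 % is a failure in Aim 3 and the Clinical section, but a success in the power statement. In the response bands the same patient is both a success and a partial responder, and a fall of exactly 10 % is both partial response and no response.

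Second, the hypothesis and the tests point in different directions. A claim of comparability needs evidence that any deficit is smaller than some stated amount. A test of difference can reject equality, but failing to reject says only that the data were insufficient to show a difference. The Background illustrates the risk: it moves from no significant difference in earlier studies to equal effectiveness, while calling those studies generally underpowered. The same step in the trial report would present comparable IOP lowering as established when it had not been tested.

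**Working it through.** **1. The plan's own figure.** The 79 % power cannot be reproduced uniquely, because no control success rate is given. With 193 per arm (the enrolment target) and a two-proportion test at 5 % two-sided:

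power = Φ[(0.10 − 1.96·SE₀)/SE₁]

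For 80 % v 90 %: SE₀ = √(2 × 0.85 × 0.15/193) = 0.0364; SE₁ = √((0.16 + 0.09)/193) = 0.0360; power = 78.8 %.

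| Assumed rates | Two-proportion power | Chance of missing a true 10-point difference |
|---|---|---|
| 80 % v 90 % | 78.8 % | 21 % |
| 70 % v 80 % | 62.2 % | 38 % |
| 60 % v 70 % | 54.0 % | 46 % |
| 50 % v 60 % | 50.6 % | 49 % |

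Log-rank approximations for 80 % v 90 %, with failure as the event, give 77.9 % (Freedman) and 81.5 % (Schoenfeld). With success as the event, 75 % v 85 % gives 78-79 %. Among assumed control rates of 40-90 %, the stated power is therefore attainable only when success is high. Taken at face value, it still means that a true 10-point difference would be non-significant 21 % of the time.

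**2. What a non-significant result leaves open.** Inputs: 193 enrolled and 15 % attrition (Sample size estimation), so 193 × 0.85 = 164 per arm at 24 months. Success rates are assumptions.

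half-width = 1.96·√(2p(1−p)/n)

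| Assumed success p | n = 164 | n = 193 |
|---|---|---|
| 50 % | 10.8 points | 10.0 points |
| 70 % | 9.9 | 9.1 |
| 75 % | 9.4 | 8.6 |
| 80 % | 8.7 | 8.0 |
| 90 % | 6.5 | 6.0 |

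An observed difference of zero leaves a deficit of one half-width inside the interval. An observed deficit just short of significance lies nearly one half-width below zero, so the interval reaches nearly two: up to 2 × 9.9 = 19.8 points at 70 % and 2 × 8.7 = 17.4 points at 80 %.

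**3. How often the cut-off matters.** Assume whole-mmHg readings; the article does not state the resolution. A fall of exactly 25 % then needs a baseline divisible by 4: 16 to 12, 20 to 15, 24 to 18, 28 to 21, 32 to 24. A fall of exactly 10 % needs a baseline divisible by 10, such as 20 to 18. Simulating baseline IOP with mean 22-26 mmHg and SD 4, and percentage reduction with mean 22-30 and SD 12 (all assumed), gives exactly 25 % in 3-4 % of patients. With 164 per arm that is 0.03 × 164 = 5 to 0.04 × 164 = 7 patients.

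These simulation inputs imply success of about Φ((22−25)/12) = 40 % to Φ((30−25)/12) = 66 %, below the 70-80 % used in step 2. The two illustrations rest on different assumptions. At the lower rates the intervals in step 2 are wider, not narrower.

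**The case against.** The strongest reply is that IOP is secondary, that the full analysis plan is not shown, and that the article already plans odds ratios and hazard ratios with 95 % confidence intervals as well as GEE of IOP itself. It nowhere says that non-significance will be read as comparability. This stands in part: the estimates needed are largely planned, and a margin could be added at little cost. It does not remove the mismatch. The article itself states the comparability hypothesis and specifies and powers only difference tests for it, so more is at issue than a detail left to another document.

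It can also be said that the response bands under Topical ocular hypotensive therapy serve treatment steps and need not share the outcome's threshold. That is fair. The direct conflict is between Aim 3 and the Clinical section on one side and the power statement on the other; the bands have their own overlaps. A tie rule applied alike in both arms would also move the difference between arms less than it moves the rates. A time-to-event analysis may use all 193 per arm, which narrows the intervals to about 8-9 points at 70-80 % success.

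Two stronger readings are tempting and are not supported.

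- A reader might infer that IOP comparability triggers the economic clause on SLT being at least as effective. The Economic analysis section defines effectiveness by AQoL-7D utilities, so that clause does not turn on IOP.
- A reader might infer that crossover under intention to treat makes comparability nearly automatic. Crossover is part of the stepped regimens and may pull the arms together. But the article gives no crossover rate, the regimen figures are not shown, and it does not say how crossover enters the IOP analysis; time-to-event endpoints may occur before it. Analysis as randomised is also a legitimate comparison of initial-treatment strategies.

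**Conclusion.** Both core defects are in the text. The IOP success outcome carries two cut-offs, and the bands that steer treatment overlap at their 25 % and 10 % boundaries. The planned tests, followed as written, cannot support the hypothesis of comparable IOP reduction.

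The cut-off conflict is small: 3-4 % of patients, under assumed distributions and whole-mmHg readings. The missing margin matters more. With 164 per arm and an assumed 70-80 % success, a null result leaves a deficit of about 9-10 points possible at an observed difference of zero, and nearly twice that when the deficit is just non-significant. The point is worth correcting but limited to a secondary claim; the primary quality-of-life superiority comparison is untouched.

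**What to change.** 1. State one definition of IOP success in Specific aims, Outcome measures (Clinical) and Sample size estimation. Reconcile the overlapping response bands under Topical ocular hypotensive therapy with it. Which threshold is clinically right is for the investigators and is not judged here.
2. Before outcome data are analysed by arm, pre-specify a justified non-inferiority margin. Conclude that IOP reduction is comparable only if the 95 % confidence interval for SLT minus drops excludes a deficit larger than the margin. The preferred measure is 24-month IOP adjusted for baseline, with the success rate alongside. Blinding cannot be the reference point for timing, because investigators and patients are unmasked.
3. If no margin can be justified, withdraw the comparability hypothesis and report the estimate with its interval.
4. Optionally, because the regimens allow crossover, report success on the assigned modality beside the intention-to-treat result. Its limit should be stated: treatment changes are partly decided by unmasked investigators and may follow adverse events or progression, so this measure does not reflect IOP alone.

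The cost is wording and one agreed margin, with no new patients or visits. The downside is that comparability on the success rate may be out of reach. Purely as an illustration, with an assumed 10-point margin, equal true rates and 164 per arm, power = Φ(0.10/SE − 1.96) is 51 % at 70 % success (SE 0.0506) and 62 % at 80 % (SE 0.0442).

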### Specific aims

Aim 1: Our first aim is to compare the effect of SLT and topical medication on glaucoma-specific QoL at 6 weeks and at 6, 12, and 24 months post-treatment (primary outcome).

Aim 2: Our second aim is to quantify the cost-effectiveness of SLT treatment compared with glaucoma medication treatment.

Aim 3: Our third aim is to determine factors associated with treatment outcomes at 12 and 24 months post-SLT, including the rate of IOP success, defined as >25 % reduction in IOP from baseline measurements.

Aim 4: Our final aim is to assess the impact of SLT and eye drops on safety, laser-linked complications, and common side effects for glaucoma patients after the initiation of treatment.

